### Sample size

Data for the South Western Ambulance Service from our pilot study shows that resuscitation for OHCA was commenced by prehospital providers in approximately 100 cases during the month. Rates of survival average 7.5%. We estimate that after application of inclusion and exclusion criteria, we will be able to include 6000 patients, of which approximately 600 will be CCT cases. This will allow us to detect an absolute improvement in survival rates of approximately 4.5% with a power of 0.8 and alpha 0.05, assuming one-to-two matching and a survival rate of 7.5% in the control group.

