Research undertaken as a pilot study for this project examined the impact of the South West Ambulance Service NHS Foundation Trust’s (SWAST) CCT on survival from OHCA [21]. This retrospective database analysis compared survival to hospital discharge between 165 cases of OHCA attended by CCTs and 1686 cases attended by ALS-paramedics. While survival was significantly higher in the CCT group than the ALS-paramedic group (15.8% and 6.5%, respectively, *p* < 0.001), this was largely due to an imbalance in prognostic factors. After adjusting for these, using multiple logistic regression, there was no significant benefit from CCT attendance in this sample (OR 1.54, 95% CI 0.89–2.67, *p* = 0.13).

Currently, all EMS in the UK dispatch paramedics trained in advanced life support (ALS) to confirmed or suspected OHCA [3]. Prehospital critical care teams (CCTs) are utilised by some but not all NHS ambulance trusts, and their availability varies significantly across regions [9, 22]. This results in large variations in the care and resources available for OHCA, possibly reflecting the uncertainty regarding the clinical benefits of CCTs [9, 23].

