### Data analysis

In participating ambulance trusts, dispatch of CCTs is via a dedicated procedure which assesses all incoming 999 calls for signs of critical illness or injury. The decision to dispatch the CCT is generally based on a combination of clinical decision making of the dispatcher and the CCT as well as fixed dispatch criteria. In some cases EMS providers will request support from a CCT after arriving on scene. Our pilot study showed that the CCT is more likely to be dispatched to OHCAs with good prognostic factors, such as an OHCA with bystander CPR in a younger patient. The overall patient group attended by a CCT therefore has more favourable prognostic factors compared to the group attended by ALS-trained paramedics. To correct for this imbalance, we will match cases of the CCT group with controls of the ALS-trained paramedic group, using propensity score matching. This method of controlling for prognostic variables in observational data has been used successfully in OHCA research recently [27, 28]. We have shown that CCTs attend approximately 10% of all OHCA cases, resulting in a large pool of controls, allowing us to match multiple controls with each case (see step 2 below).

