Propensity score matching will involve the following steps [29]:We will run a logistic regression with CCT attendance as the dependent variable. Prognostic factors for both survival to hospital discharge and CCT dispatch will be covariates. They will include age and gender of the patient, the cause and location of OHCA, whether it was witnessed, bystander CPR, ambulance response time, first recorded rhythm and distance from CCT base. This will allow us to calculate a propensity score for each patient - the probability of the patient receiving CCT treatment.We will then match each CCT case with ALS-trained paramedic cases of OHCA, with similar propensity scores. This will be done using nearest neighbour matching within a specified calliper distance - the ‘greedy algorithm’ assigns controls with similar propensity scores to each case. To qualify as 'matching' the propensity score of potential controls needs to be within 0.2 of the pooled standard deviation of the logit of the propensity score [30]. This reduces the risk of bias from matching controls to cases whose propensity scores differ too much. To optimise available data, we will match each CCT case with up to five ALS-paramedic controls whose propensity scores are within the defined caliper, accepting varying numbers of controls per case. Each control will only be available for matching once and then will be removed from the control pool [31].We will compare the matched CCT and ALS-paramedic groups to verify that prognostic factors are balanced between the groups.We will analyse for statistically significant differences in survival to hospital discharge between the groups (see also ‘3.2.5 data analysis’).

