The matching process will result in two groups of OHCA patients: an intervention group that has been attended by a CCT in addition to the usual ambulance response, and a control group that has been attended by ALS-trained paramedics alone. We will compare the primary outcome of survival to hospital discharge between OHCA attended by the CCT and OHCA attended by ALS-trained paramedics. We will conduct multivariable logistic regression analyses for the full cohort and conditional logistic regression for the propensity score matched groups. We will also undertake subgroup analysis for witnessed OHCA with shockable rhythm, with the hypothesis that any potential benefit of CCT attendance will be more pronounced. There is a possibility that any observed benefit from CCT care is due partially to CCTs conveying more patients to a cardiac centre, bypassing nearer hospitals. We will therefore also compare the secondary outcome of survival to hospital admission.

In addition, we will describe the frequency of prehospital critical care interventions delivered by the CCTs for OHCA. We will then undertake logistic regression analysis including known predictors of survival, with the individual critical care interventions as independent variables and survival to hospital discharge as a dependent variable. We estimate that there will be enough survivors of OHCA to allow multiple logistic regression with up to ten variables (estimated 100 survivors, with 10 outcomes per variable). However, should this not be possible, we will describe frequency of critical care interventions occurring during OHCA treatment, which will be useful information when interpreting the overall results of this project.

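### The power statement gives matched controls the all-case survival rate of 7.5%, whereas the protocol's own pilot implies about 11%; the stated 4.5 points should be restated for the matched comparison

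*Protocol article*

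**What the plan says.** The Sample size section first reports "Rates of survival average 7.5" per cent in the pilot ambulance service, without separating CCT from ALS cases. It then expects that "we will be able to include 6000 patients, of which approximately 600 will be CCT cases", and concludes that this will "detect an absolute improvement in survival rates of approximately 4.5% with a power of 0.8 and alpha 0.05". The basis given for that figure is a calculation "assuming one-to-two matching and a survival rate of 7.5% in the control group".

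Three other statements bear on those inputs:

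- The Data analysis section explains why matching is needed: "The overall patient group attended by a CCT therefore has more favourable prognostic factors" than the ALS group.
- The same section describes the matching itself: "we will match each CCT case with up to five ALS-paramedic controls", within a caliper, without replacement, and with the number of controls allowed to vary from case to case.
- The Background account of the pilot says that "survival was significantly higher in the CCT group than the ALS-paramedic group (15.8% and 6.5%, respectively"). It attributes most of that gap to prognostic imbalance and gives an adjusted OR of 1.54 (95% CI 0.89–2.67), from 165 CCT and 1686 ALS cases.

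**The concern.** Propensity matching selects ALS patients who resemble CCT patients. CCT patients have the better prognosis, so their matched controls should survive more often than the average case. The power calculation nevertheless gives those controls the average rate. For a fixed absolute difference, a control rate moving up from 7.5% towards 16% increases the binomial variance and lowers power.

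The stated figure matters for interpretation. The abstract's Discussion says that, if no benefit is found, charities may consider moving effort to other areas of prehospital care. A null result would be read against 4.5 points at 80% power, so that figure should describe the comparison actually made.

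**Working it through.** **Inputs.** 600 CCT cases, ratio 1:2, control survival 7.5%, difference 4.5 points, alpha 0.05 and power 0.80 come from Sample size. The maximum of five controls comes from Data analysis. The pilot sizes, survival rates and adjusted OR come from the Background. The protocol does not state sidedness; two-sided is assumed.

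**Method.** Two independent proportions, normal approximation. With n₁ CCT cases, n₂ = r·n₁ controls, d = p₁ − p₂ and p̄ the weighted mean rate:

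- SE₀ = √[p̄(1−p̄)(1/n₁+1/n₂)] and SE₁ = √[p₁(1−p₁)/n₁ + p₂(1−p₂)/n₂]
- pooled: power = Φ[(d − 1.96·SE₀)/SE₁]
- unpooled: power = Φ[d/SE₁ − 1.96]

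The ranges below span the two versions. The detectable difference is the d that gives power 0.80.

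**Step 1: the plan's own figure.** p₁ = 0.120, p₂ = 0.075, n₁ = 600, n₂ = 1200, so p̄ = (72 + 90)/1800 = 0.090, SE₀ = 0.01431 and SE₁ = 0.01529.

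- Pooled: (0.045 − 0.02805)/0.01529 = 1.11, power 86.6%.
- Unpooled: 0.045/0.01529 − 1.96 = 0.98, power 83.7%.
- Detectable difference at 80%: 4.05 (pooled) to 4.26 (unpooled) points.

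Continuity-corrected (84.8%), arcsine (86.3%), simulated Fisher (about 84.7%) and one-sided (92.0%) versions do not return 80% either. The stated 4.5 points corresponds to about 500 CCT cases at 1:2 (496 by the pooled formula). It is therefore cautious on its own inputs.

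**Step 2: where 7.5% comes from.** The pilot groups pool to (165 × 15.8% + 1686 × 6.5%)/1851 = 7.3%, which confirms that 7.5% is an all-case figure.

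**Step 3: survival implied for matched controls.** CCT odds are 0.158/0.842 = 0.1876. Dividing by the adjusted OR:

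| Adjusted OR | Control odds | Control survival |
|---|---|---|
| 1.54 | 0.1218 | 10.9% |
| 2.67 (upper limit) | 0.0703 | 6.6% |
| 0.89 (lower limit) | 0.2108 | 17.4% |

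If CCT attendance has no effect, matched controls would survive at the CCT group's own rate, 15.8%.

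**Step 4: power for +4.5 points and detectable difference, 600 CCT cases.**

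| Control survival | Ratio | Power for +4.5 points | Detectable at 80% (points) |
|---|---|---|---|
| 7.5% | 1:2 | 84–87% | 4.05–4.26 |
| 10.9% | 1:2 | 74–77% | 4.7–4.9 |
| 10.9% | 1:3 | 78–82% | 4.4–4.6 |
| 10.9% | 1:5 | 81–86% | 4.1–4.4 |
| 15.8% | 1:2 | 64–66% | 5.4–5.5 |
| 15.8% | 1:5 | 72–76% | 4.8–5.0 |

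These are unmatched formulas. The matched analysis is conditional logistic regression, and the protocol gives no within-set correlation from which to compute its power directly.

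**The case against.** **The departures offset, so the figure survives.** This largely stands. With 10.9% control survival and two to five controls per case, power for 4.5 points runs from 74% to 86%, which brackets 80%. A reader might infer that the study is underpowered for 4.5 points. The protocol does not support that: it would require a mean ratio near 1:2 or lower, many unmatched CCT cases, or control survival well above 11%.

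**One-to-two is not an error.** This stands. Caliper matching without replacement will leave some cases with fewer than five controls, so planning on two may be deliberate caution. A planning value of two is compatible with a ceiling of five.

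**The 11% is imprecise.** This stands too. It rests on 165 CCT cases and a wide interval, and it applies a conditional OR to a marginal rate. The value 7.5% lies inside 6.6–17.4%. But the section does not present 7.5% as a matched-control estimate; it is an overall average, and the pilot's point estimate is higher.

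**The planned model tests an odds ratio.** Going from 7.5% to 12% is an OR of 1.68. The same OR at 10.9% leads to 17.0%, for which power at 1:2 is 93–95%. That is correct, but the protocol states its target in absolute points, and on that scale the loss of power is real.

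**Apparent conflict over CCT survival.** A reader might also set the 12% implied by the power statement (72 of 600) against the Data analysis figure ("estimated 100 survivors, with 10 outcomes per variable") and infer a contradiction. There is none. The 12% is a control rate plus a detectable difference. The 100 is a forecast of events for a separate regression and, if it refers to CCT cases, is close to 600 × 15.8% = 95. The two need not agree.

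**Conclusion.** The control rate in the power statement belongs to the wrong population, and the stated 4.5 points does not follow even from the inputs given. Putting 10.9% in place of 7.5% at the stated 1:2 ratio lowers power for 4.5 points by about 10 percentage points, to 74–77%; a full 1:5 ratio brings it back to 81–86%. That the stated figure lies near the corrected range is the result of departures that offset each other, not of a calculation for the planned comparison.

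The conclusion assumes two-sided alpha of 0.05, 600 matched CCT cases, the pilot's point estimates and an unmatched approximation. It is a correction to a figure used for interpretation. It does not bear on the analysis method or the recruitment target.

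**What to change.** Rewrite the sample-size sentence for the matched comparison:

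- Give matched-control survival as about 11%, show its derivation from the pilot, and report the range 6.6–17.4%.
- Keep 600 CCT cases, and state the expected mean number of controls per case, between two and five. If 1:2 is deliberate caution, say so.
- State sidedness and the formula used.
- Report a detectable difference of about 4.1–4.9 points at 80% power, rising to about 5.5 at 1:2 if controls survive at 15.8%.

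The cost is one paragraph and a slightly less favourable figure at 1:2. No extra patients are needed and no analysis changes.

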### Stakeholder-focused cost analysis

A cost analysis of prehospital critical care for OHCA will be undertaken for the South Western Ambulance Service NHS Foundation Trust (SWAST). We will follow a previously published and validated structure for cost analyses of EMS [32]. The toolkit treats resource use and prices separately from a societal perspective. Cost analysis is undertaken using the following steps:Define the community for which costs are being calculatedDetermine all of the agencies that are part of the EMS systemEstimate the percentage of time that each agency is involved in EMSCalculate human resource costsCalculate physical plant costsCalculate vehicle costsCalculate equipment costsCalculate other administrative costsCalculate EMS-related training costsCalculate bystander training costsCalculate any costs associated with revenue generation

The necessary data for the cost calculations are available from routine billing documents of SWAST and the Great Western Air Ambulance Charity. Other important information, such as average number of paramedics and vehicles dispatched to OHCA and time spent with each case will be extracted from the SWAST OHCA database and routinely collected data. We will calculate the costs of providing ALS-trained paramedic prehospital care for OHCA and the incremental costs of providing physician-led prehospital critical care. Combining this incremental cost with the impact of CCTs on survival to hospital discharge after OHCA will allow decision-makers in EMS and the public donating money to air ambulance charities to assess the cost-effectiveness of prehospital critical care for OHCA. In addition to the total incremental costs of CCTs, we will also present the costs currently covered by charities and those currently covered by NHS organisations. We will also differentiate between costs caused by utilisation of a helicopter and use sensitivity analysis to estimate the impact of transport modality on overall costs. Our approach to costing is pragmatic. We will not describe the costs of in-hospital or post-discharge treatments, as they are unlikely to influence stakeholders in EMS commissioning.

## Discussion

The overall aim of this research project is to guide the commissioning of prehospital care for OHCA. As such, the research focuses on the clinical effect of prehospital critical care teams, as well as its costs, as far as EMS spending is concerned. In the UK, a large part of prehospital critical care is currently supported by the public, through donations to charities. Understanding how these different groups support and interpret relevant research is therefore important to maximise the impact of future research.

The ideal outcome to measure the success of prehospital interventions for OHCA is unclear. Early outcomes such as ROSC, while generally clearly attributable to EMS interventions, are not patient-focused and can overestimate the actual benefits of interventions that might only prolong the interval between OHCA and the patient’s subsequent unavoidable death [4]. The ideal patient-focused outcome after OHCA would be long-term survival with good neurological function [33]. The disadvantages of using this outcome are the resources required to record it as well as loss of patients to follow up. In addition, patients with long term survival will have spent minutes in the EMS, followed by days in hospital, which raises the issue of differences in hospital treatment confounding results [33, 34]. As a pragmatic approach, we chose survival to hospital discharge as the primary outcome, and survival to hospital admission as a secondary outcome. Survival to hospital discharge in the UK is associated with a high likelihood of survival with normal or mildly impaired neurological status (89% in a study of 1476 patients admitted to hospital after OHCA) [35]. We therefore consider it a satisfactory surrogate outcome for this study.

The research is designed as a multicentre study, which will help generalisability. The different prehospital critical care services participating in this research will all have slight variation in their deployment (helicopter and/or rapid response vehicle) and the interventions that are used when treating OHCA. After review of local and regional practice, we are assured that these differences are not large enough to limit the generalisability of our findings. In fact, the variation in interventions between cases of OHCA treated within the same CCT observed in our pilot analysis is much more significant, ranging from zero to eight critical care interventions per case. To account for these variations, we will record all critical care interventions delivered for each case.

This research aims to inform relevant stakeholders in prehospital care of the effects and costs of prehospital critical care following OHCA. Together with a detailed description of critical care interventions undertaken during the care of patients who suffer OHCA, this information can guide future practice and funding of prehospital care for OHCA. The results will be made publicly available on an open access website, and we will publish the findings in appropriate journals and present them at national and international conferences relevant to the subject field.

## Abbreviations

ALS: Advanced life support
CCT: Critical care team
CPR: Cardiopulmonary resuscitation
EMS: Emergency Medical Service
OHCA: Out-of-hospital cardiac arrest
ROSC: Return of spontaneous circulation
SWAST: South Western Ambulance Service NHS Foundation Trust
UK: United Kingdom
